### Primary outcomes

The primary outcomes include the feasibility of the study and longitudinal changes from baseline to mid- and end-of-intervention, assessed in muscle function (VO_2_peak and one-repetition maximum strength), muscle mass using ultrasound imaging, cognitive function using the NIH Toolbox Fluid Composite score, and immune function using the CD4/CD8 T cell ratio as indicated in the XPRIZE guideline (version 2.0) [20].

#### Feasibility assessment

The feasibility of the interventions is assessed based on six parameters:Participation rate, defined as the percentage of eligible participants included in the study at registration, pre-screening, and screening.Dropout rate, defined as the percentage of participants who withdraw during the study period, along with the reasons for withdrawal.Adherence to the sleep intervention, expressed as the total number and percentage of nights with ≥ 7 h of sleep time as recorded using a wearable device for continuous monitoring.Adherence to the supplementation intervention assessed at each study visit and calculated as the amount of supplements consumed divided by the total amount prescribed. The amount consumed is determined as the difference between the amount of supplement dispensed and the amount returned by the participants. Adherence is expressed as the total amount and percentage of supplements consumed.Adherence to the exercise intervention, expressed as the total number and percentage of aerobic and strength training sessions and exergaming sessions attended as recorded by the researcher.Adherence to dietary recommendations assessed by the 3-day food diary at baseline and end-of-intervention and the subsequential nutritional analysis.

Protocol adherence was monitored through weekly check-in to track the intervention components, including exercise attendance, supplement intake, and dual-task exercise training engagement. Overall feasibility will be assessed based on the above mentioned six feasibility parameters, which will be used as categorical variables and dichotomised based on their distribution using a cut-off point of 80%.

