Supervised multicomponent exercise training was conducted three times per week, with each session lasting approximately 60 min. Each session includes a warm-up, resistance training, and endurance training and concludes with dual-task cognitive–physical training. Resistance training included two sets of 8–15 repetitions across five exercises (plate-loaded seated leg extension, pin-loaded seated row, pin-loaded latissimus pulldown, barbell bench press, and dumbbell lateral raise) performed on resistance exercise machines, with a 2-min rest interval between sets. Training loads were progressively adjusted throughout the intervention to maintain the repetition range while ensuring continued overload. Endurance training was performed on a stationary bike starting at Zone 2 intensity (heart rate reserve 50–60%) and progressing to Zone 3 intensity (heart rate reserve 60–70%). Heart rate was continuously monitored using a Polar arm-band heart rate monitor (Polar Electro Oy, Kempele, Finland). At the end of the session, dual-task cognitive-physical training was performed using digital tools, including exergames and applications such as NeuroTrackerX (CogniSens Athletics Inc., Canada), SportReact reaction lights (SportReact, Croatia), SwitchedOn (SwitchedOn LLC, USA), and ClockYourself (Clock Yourself Pty Ltd., Australia). Training focused on memory and balance in the first session of each week, processing speed and motor skills in the second session of each week, and executive function and mobility in the third session of each week. Sessions were periodised and programmed to be progressively increased both in terms of physical and cognitive load.

Participants received whey protein supplementation (GOLD STANDARD 100% ISOLATE Chocolate Bliss, Optimum Nutrition, Illinois, USA) using the standard 30 g scoop as supplied by the company (each delivering ~ 25 g of protein). The dosage is adjusted according to the body weight categories as follows: 40–59 kg: 1 scoop/day, 60–89 kg: 1.5 scoops/day, and 90 kg and above: 2 scoops/day [25]. In addition, participants took micronized monohydrate creatine supplementation (1.25 g per capsule Optimum Nutrition, Illinois, USA) according to the body weight categories (40–59 kg: 4 capsules/day, 60–89 kg: 6 capsules/day, 90 kg and above: 8 capsules/day) [26] and fucoidan (2.4 g/day, SIRT6Activator®, DoNotAge.org, USA) [27].

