### Statistical and analytical plans

Adherence to each intervention component (sleep, dietary recommendation, supplementation, and exercise) will be analysed descriptively. Adherence will be summarised across the intervention period using mean and standard deviation (SD) or median and interquartile range (IQR) where appropriate. Adherence will be additionally categorised using a predefined threshold of ≥ 80% to indicate adequate adherence. The proportion of participants meeting this threshold will be reported for each intervention component.

Changes in outcome measurements at the mid-intervention and the end-of-intervention compared to baseline will be calculated for each participant. Continuous outcomes will be summarised as mean changes with 95% confidence intervals (CIs) for approximately normally distributed data or as median changes with interquartile ranges (IQRs) for non-normally distributed data. Within-participant changes from baseline to each follow-up timepoint will be assessed using paired t-tests or Wilcoxon signed-rank tests, as appropriate.

To evaluate longitudinal changes across all study timepoints while accounting for within-participant correlation, linear mixed-effects models will be applied for continuous outcomes. Timepoint will be included as a fixed effect, and participant ID will be included as a random effect. Estimated marginal means and corresponding 95% CIs will be reported for each timepoint, together with model-based contrasts comparing mid- and end-of-intervention with baseline.

To account for multiple testing across outcome measures, the Benjamini–Hochberg procedure will be applied to control the false discovery rate. All statistical tests will be two-sided, given the small sample size (*n* = 20), *p* values will be interpreted descriptively and hypothesis-generating only, and 95% CIs will be reported where applicable to support estimation of effect magnitude and precision.

Data will be visualized in spaghetti plot to display the changes during the intervention trajectory at individual level and the group level. All data analysis and visualization will be performed using R.

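### Supplement adherence is a single ratio with no stated unit and no split by product, so complete non-use of a personalised supplement can still pass the 80% threshold

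*Protocol article*

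**What the plan says.** The Feasibility assessment section of the protocol article lists supplement adherence among six feasibility parameters, and feasibility is part of the primary outcome. The parameter is "calculated as the amount of supplements consumed divided by the total amount prescribed". Consumption is "the difference between the amount of supplement dispensed and the amount returned by the participants", and the result is reported in one form: "Adherence is expressed as the total amount and percentage of supplements consumed".

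The Statistical and analytical plans section keeps supplementation as one of four components: "Adherence to each intervention component (sleep, dietary recommendation, supplementation, and exercise) will be analysed descriptively". It then sets the cut-off, "Adherence will be additionally categorised using a predefined threshold of ≥ 80% to indicate adequate adherence", and the level of reporting, "The proportion of participants meeting this threshold will be reported for each intervention component".

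The article does not say in what unit an amount is measured or how scoops, capsules and tablets are combined. It asks for no adherence figure by product and none for fundamental and augmented supplements separately. The exercise parameter in the same list, by contrast, does name its parts (aerobic and strength sessions, and exergaming).

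**The concern.** What distinguishes this trial is the augmented intervention: urolithin A, NMN and a multivitamin-multimineral assigned from baseline assessments, with dose increases or added ergothioneine at week 4. Whether participants take these products is a central feasibility question, and the trial is meant to inform a 12-month randomised trial.

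The prescribed products differ greatly in bulk. Whey is dosed in tens of grams a day ("using the standard 30 g scoop as supplied by the company", at 1 to 2 scoops), while NMN starts at 300 mg a day. One ratio across all of them gives each product a weight that depends on the unit chosen, not on its role in the design. A participant could pass on supplementation without taking any of the tailored part. It would also be harder to tell non-response from non-intake when interpreting the week-4 adjustments.

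**Working it through.** The article reports no adherence figure to reproduce, so the check scores a hypothetical participant who takes every fundamental supplement and none of the augmented ones.

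**Inputs** (Fundamental interventions, Augmented intervention, Table 3), in g/day for the three body-weight bands 40–59, 60–89 and ≥ 90 kg:
- Whey powder, 30 g per scoop at 1, 1.5 and 2 scoops: 30, 45, 60.
- Creatine, 1.25 g per capsule at 4, 6 and 8 capsules: 5, 7.5, 10.
- Fucoidan: 2.4, or 3.6 if increased at week 4.
- Augmented at baseline: urolithin A 0.5 + NMN 0.3 + multivitamin tablet 1.2 = 2.0.
- Augmented at full escalation: 1.0 + 0.6 + 1.2 + ergothioneine 0.011 (3 × 25 mg = 75 mg a week, divided by 7) = 2.811.

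**Pooling by mass (assumed).** Score = fundamental amount taken / (fundamental + augmented amount prescribed).

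| Weight band | Baseline doses | Full escalation, fucoidan taken at 3.6 g | Full escalation, added 1.2 g fucoidan also skipped |
|---|---|---|---|
| 40–59 kg | 37.4/39.4 = 94.9% | 38.6/41.41 = 93.2% | 37.4/41.41 = 90.3% |
| 60–89 kg | 54.9/56.9 = 96.5% | 56.1/58.91 = 95.2% | 54.9/58.91 = 93.2% |
| ≥ 90 kg | 72.4/74.4 = 97.3% | 73.6/76.41 = 96.3% | 72.4/76.41 = 94.8% |

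The last two columns apply to weeks 5–8. Over 8 weeks (four at baseline doses, four fully escalated with fucoidan taken) the scores are 94.0%, 95.8% and 96.8%. With only one baseline augmented product prescribed and skipped, the range is 37.4/38.6 = 96.9% (multivitamin, lowest band) to 72.4/72.7 = 99.6% (NMN, highest band). Counting whey as 25 g of protein per scoop, the lowest figure in any scenario is 35 g-based: (25 + 5 + 2.4)/(25 + 5 + 3.6 + 2.811) = 32.4/36.41 = 89.0%. Every mass scenario passes 80%.

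**Counting dose units.** The article does not give the number of capsules for fucoidan, urolithin A or NMN. Assume 1–8 fucoidan capsules a day and 1–2 capsules each of urolithin A and NMN, at baseline prescription.
- All three augmented products skipped, lowest: (1 + 4 + 1)/(6 + 5) = 54.5%.
- All three skipped, highest: (2 + 8 + 8)/(18 + 3) = 85.7%.
- Only the multivitamin prescribed and never taken, with at least one fucoidan unit a day: at least (1 + 4 + 1)/(6 + 1) = 6/7 = 85.7%.

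**Unweighted mean over products.**
- Six products prescribed, all three augmented ones skipped: 3/6 = 50%.
- Six prescribed, one augmented product skipped: 5/6 = 83.3%.
- Four prescribed, the single augmented one skipped: 3/4 = 75%.

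For total non-use of three prescribed augmented products at baseline doses, the score thus runs from 50% to 97.3% depending on a choice the article does not state. Non-use of one product can pass under all three conventions.

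**The case against.** The strongest objection is that mass pooling is not in the document. A reader might infer that the measure is in effect a whey measure, that anyone ignoring the augmented products necessarily scores 95–97%, or that skipping whey alone drops a participant to 19–24% (9.4/39.4 = 23.9% down to 14.4/74.4 = 19.4%). The article supports none of these unconditionally, because they hold only if grams are added. In dose units, under the assumptions above, skipping whey leaves about 86–94%, and skipping all augmented products gives about 55–86%. Consumption is also described for a supplement in the singular, which is compatible with counting product by product, and elsewhere in the same list a total means a sum over the period. This part of the objection stands.

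It can also be said that a condensed article leaves tabulation details to the full protocol or analysis plan. That has some force for the unit. It has less force for the structure, because the article itself states the formula, the single component and the threshold. Nothing in it excludes product-level tables, but nothing calls for them either.

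Finally, adherence is analysed descriptively and the article ties no go/no-go rule to this figure. That limits the severity but does not remove the defect.

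**Conclusion.** The point holds in a conditional form. The definition combines all supplements without a unit or product split. If pooled by mass, complete non-use of all three baseline augmented products passes at about 95–97% (about 93–96% at full escalation, about 90–95% in weeks 5–8 with the added fucoidan also skipped). Under dose units the result for the same participant can fall on either side of 80%, and under a six-product mean it fails at 50%. Even so, complete non-use of a single personalised product can pass, for example at 85.7% or 83.3%. A pass on this parameter therefore does not show that the personalised supplements were taken.

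The figures rest on full intake of the remaining supplements, on the doses in the article and, for dose units, on assumed capsule counts. Severity is moderate: the parameter belongs to a primary outcome, but the analysis is descriptive and can still be corrected from dispensing and return data.

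**What to change.** State the unit, and compute adherence per product as units consumed divided by units prescribed. Use the dose in force in each 4-week period, and account for any change or cessation directed by the investigator. For each product, report the percentage consumed and the proportion of participants prescribed it who reach 80%. Summarise fundamental and augmented supplements separately. Requiring 80% on every prescribed product is one possible participant-level summary; it is optional, and it becomes harder to meet as more products are prescribed.

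The cost is a little re-tabulation of dispensed and returned amounts, assuming these were recorded by product. The reported adherence may come out lower than a pooled figure. The article describes analysis as ongoing, so the definition can be settled and documented before results are reported.

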#### Muscle function assessments

VO_2_peak was measured using a graded exercise test conducted on a cycle ergometer. The participants first performed a standardised warm-up (5 min at 30 W). Then, the participants performed an incremental ramp protocol during which resistance was progressively increased by 1 W every 2 s until exhaustion occurred, which was defined as the point when cycling cadence fell below 60 rpm. Gas exchange and heart rate were continuously monitored throughout the test [46].

Lower limb muscle strength was evaluated using one-repetition maximum (1RM) test on the leg extension machine. Participants completed warm-up sets at 50%, 75%, and 95% of their estimated 1RM for 8–10, 3–5, and 1 repetition, respectively. Participants then performed 1RM attempts with increasing loads until they were unable to complete the lift through the full range of motion. A 3-min rest period was provided between sets.

#### Muscle mass assessment

Muscle thickness and intramuscular fat infiltration (IMAT) are assessed using a portable B-mode ultrasound system (Philips Lumify Ultrasound System) equipped with a high-frequency linear array transducer (4–12 MHz). All scans were performed by trained operators following a standardised acquisition protocol. Participants were in supine position for all measurements. For lower limb assessments, the rectus femoris and vastus lateralis were imaged at the midpoint between the anterior superior iliac spine and the superior border of patella, with the vastus lateralis assessed on the lateral aspect of the thigh. At least two high-quality images were acquired at each muscle site and subsequently analysed using the MuscleSound software (Denver, CO, USA).

#### Cognitive function assessment

Cognitive performance was evaluated using the NIH Toolbox Cognition Battery (fluid cognition composite score and age-corrected percentage score in the population) [47] administered via a tablet, and conducted in a quiet room with no distractions, and only one researcher was allowed to carry out the assessment. The composite measure captures subdomains including working memory, attention, executive function, episodic memory, and processing speed [22].

#### Immune function assessment

Immediately after venipuncture, 250 μL of fasting fresh whole blood was aliquoted from the K2-ethylenediaminetetraacetic acid (K2-EDTA) tube (Greiner Bio-One, Kremsmünster, Austria) for assessment of immunosenescence by quantifying the CD4/CD8 T cell ratio using BD TruCount™ tubes in conjunction with a BD CD4/CD8 reagent cocktail (Becton Dickinson, Franklin Lakes, NJ, USA), in accordance with the manufacturer’s instructions. Data acquisition was performed on a BD LSRFortessa™ Symphony A5 flow cytometer (BD Biosciences, San Jose, CA, USA), and data were analysed using FlowJo™ software (FlowJo, LLC, Ashland, OR, USA).

### Secondary outcomes

The secondary outcomes include the longitudinal changes from baseline to mid- and end-of-intervention in the biological, clinical, and digital biomarkers of ageing covering physical and mental health.

#### Biological sample collection and analysis

From overnight fasting peripheral blood drawn at each study visit, five fractions were collected: whole blood, serum, plasma, peripheral blood mononuclear cells (PBMCs), and buffy coat. Blood samples collected in K2-EDTA tubes and serum separator tubes (SST™) (BD Vacutainer®, Becton Dickinson) were centrifuged at 1200 × g for 15 min with soft brake to obtain plasma and serum, respectively. Prior to centrifugation, whole blood was aliquoted from the K2-EDTA tube and will be used for the measurement of nicotinamide adenine dinucleotide (NAD) concentrations using the Q-NADMED Blood NAD + and NADH Assay Kit (NADMED Ltd., Helsinki, Finland), according to the manufacturer’s instructions. Plasma will be used for proteomics profiling using SomaScan® 11 K Assay (SomaLogic Operating Co., Boulder, CO, USA). Untargeted metabolomics in plasma will be performed using a Vanquish UHPLC system coupled to an Orbitrap Exploris™ 120 high-resolution mass spectrometer (Thermo Fisher Scientific, Germany), with chromatographic separation on a Hypersil Gold column (100 × 2.1 mm, 1.9 μm; Thermo Fisher Scientific, USA) and an ACQUITY UPLC BEH Amide column (Waters, Ireland). Serum was collected for quantification of cytokines interleukin-6 (IL-6), IL-10, tumour necrosis factor-alpha (TNF-α), and IL-1β using the Cytokine 4-Plex A assay (Quanterix, Billerica, MA, USA) according to the manufacturer’s instructions, with detection performed by multiplex immunoassays on the Luminex® xMAP® platform (Luminex Corporation, Austin, TX, USA). Biochemical blood tests, comprising haematology, liver and renal function profiles, lipid profile, glucose, glycated haemoglobin (HbA1c), insulin, and high-sensitivity C-reactive protein (hs-CRP), were conducted by an accredited clinical laboratory. The neutrophil-to-lymphocyte ratio (NLR) was derived from biomedical blood tests to assess systemic inflammatory status. The PBMCs were isolated from whole blood collected in acid citrate dextrose solution A (ACD-A) tubes (BD Vacutainer®, Becton Dickinson) through density-gradient centrifugation using Ficoll-Paque™ PLUS (Cytiva, Marlborough, MA, USA), cryopreserved in foetal bovine serum (FBS) (Gibco, Thermo Fisher Scientific, Waltham, MA, USA) containing 10% dimethyl sulfoxide (DMSO) (Sigma-Aldrich, Merck KGaA, Darmstadt, Germany), and stored in liquid nitrogen for downstream immune-function assays.

Cryopreserved PBMCs were thawed and rested for 2–4 h at 37 °C, 5% CO₂ in complete RP-10 medium comprising RPMI-1640 supplemented with 10 mM L-glutamine, 10% FBS, 100 U/mL penicillin, 100 µg/mL streptomycin, and 10 mM HEPES (all Gibco). Cells were seeded at 2 × 10^5^ cells/well in 96-well U-bottom plates (Corning, NY, USA) and stimulated with 1 µg/mL CEF peptide pool (cytomegalovirus, Epstein-Barr virus, and influenza virus) to assess antigen-specific memory T cell responses. Vehicle control (< 0.1% DMSO) and positive control using Dynabeads® Human T-Activator CD3/CD28 (Gibco) at a 1:1 bead-to-cell ratio were included. After 24 h of incubation, supernatants were collected following centrifugation at 400 × g for 5 min. Interferon-gamma (IFN-γ) levels were quantified in the supernatants using a Human IFN-γ ELISA kit (Invitrogen, Thermo Fisher Scientific, Waltham, MA, USA) and read at 450 nm on an Infinite 200 PRO M Plex plate reader (Tecan, Switzerland). Immunophenotyping will be performed in the cryopreserved PBMCs to evaluate immunosenescence status.

Buffy coat fractions were isolated from the whole blood for genomic DNA extraction using QIAamp® DNA Blood Mini Kit (Qiagen, Germany) following the manufacturer’s instructions. Genomic DNA purity was assessed using NanoDrop™ spectrophotometer (Thermo Fisher Scientific, USA), with acceptable samples defined by an A260/A280 absorbance ratio between 1.6 and 2.1. DNA concentration was measured using Qubit™ 4.0 Fluorometer (Thermo Fisher Scientific, USA). DNA methylation profiling was conducted using the Infinium® MethylationEPIC v2.0 BeadChip (Illumina, San Diego, CA, USA) following the Infinium® HD Assay protocol. Briefly, 500 ng of the genomic DNA underwent bisulfite conversion, during which unmethylated cytosines were deaminated to uracils, while methylated cytosines remain unchanged. The converted DNA was then amplified, enzymatically fragmented, precipitated, and resuspended in hybridization buffer prior to hybridization onto the BeadChip, where locus-specific probes interrogated over 935,000 CpG sites at single-base resolution. After hybridization, non-specific DNA was removed through washing, followed by single-base extension with fluorescent labelling. BeadChips was then scanned using the Illumina iScan System (Illumina, San Diego, CA, USA), and DNA methylation levels were quantitatively determined based on the resulting fluorescence signals. DNA methylation age will be derived, including PCHorvathAge, PCHannumAge, PCGrimAge, PCPhenoAge [48], GrimAge2 and GrimAge2 surrogates [49], DunedinPACE [50], Ying clocks [51], and SystemsAge [52].

Stool samples were collected using the DNA/RNA Shield™ Fecal Collection Kit (Zymo Research, USA), which preserves and stabilizes microbial nucleic acids at ambient temperature during collection and transport. Participants received a stool collection kit along with written instructions, where they were asked to return the samples within 24 h of collection. Samples were stored in a − 20 °C freezer upon receiving. Short-read shotgun metagenomics sequencing will be performed to characterize gut microbiome composition and functional capacity. Genomic DNA will be extracted from each sample using a Maxwell® HT Fecal Microbiome DNA Kit (Promega Corporation, Madison, WI, USA) according to the manufacturer’s instructions. Extracted genomic DNA will be quantified using a fluorometric method with the Qubit™ dsDNA HS Assay Kit (Thermo Fisher Scientific, Waltham, MA, USA), and its integrity will be assessed using 1% agarose gel electrophoresis. For shotgun metagenomic library preparation, 1 μg of genomic DNA will be randomly fragmented to an average size of approximately 350 base pairs (bp) using a high-throughput focused-ultrasonicator (Covaris, Woburn, MA, USA). Sequencing libraries will be prepared using the Universal DNA Library Prep Kit for Illumina® V3 (Vazyme Biotech, Nanjing, China), following standard procedures including end repair, A-tailing, sequencing adaptor ligation, purification, and polymerase chain reaction (PCR) amplification. Libraries passing quality control will be carried forward for sequencing. Following library construction, fragment size distribution and library integrity will be evaluated using Advanced Analytical Technologies, Inc. (AATI) fragment analysis (Agilent Technologies, USA). Libraries with the expected insert size will be quantified by quantitative PCR. Qualified libraries will be pooled based on effective concentration and target sequencing depth, and sequencing will be performed on the Illumina NovaSeq X Plus platform (Illumina, San Diego, CA, USA) using paired-end 150 bp (PE150) chemistry. Taxonomic and functional annotation will be performed using DIAMOND software [53].

All excess plasma, serum, buffy coat, PBMCs, and stool samples were biobanked for future research subjected to IRB approval and participant consent.

